### 2.4. Sample Size

The ESSOC is made up of a series of measurements for each population study group (general, zones and +55) with a total of 22,000 effective interviews being carried out over three years. As of June 2021, almost 13,000 effective interviews have been conducted.

During the first measurement (M1), the ESSOCgeneral scope started with a random ‘teorical’ sample comprised of 5000 people. This sample includes respondents and non-respondents for whatever the reason for not responding. Its sample size was calculated under the assumptions of maximum variability in the estimate (p = q = 0.5), a precision of 2.4 percentage points for estimates in Andalusia, a confidence level of 95%, a non-response rate of 40% (whatever the reason) and a design effect of 1.8. The subsequent measurements (M2–M5) are comprised of the longitudinal theorical samples of the previous measurements and, in addition, of a new theorical sample in each measurement. That new theoretical sample is selected according to the design of the first measurement, except for M5 which will incorporate a new stratum of ‘residing or not in disadvantaged areas’ [60]. Finally, due to non-response, from these longitudinal and new theoretical samples an ‘effective sample’ is obtained for each measurement. Thus, those effective samples include just the respondents. With respect to the theoretical sample size for the longitudinal sample of a measurement, this is defined by the effective longitudinal sample and the effective new sample from the previous measurement. To maintain the effective sample size provided by the first measurement of the ESSOCgeneral, the aim for the subsequent ones is to reach an effective sample about 3000 people per measurement, while the effective sample size for ESSOCzones has been established at 2750 people and at least 1350 for ESSOC + 55, assuming theoretical response rates of 60% (considering all types of indidents).

Sample size for the first measurement of the ESSOCgeneral was estimated according to a non-response rate of 40% (Figure 1). This response rate was considered as the percentage of surveys carried out or effective sample with respect to the total of the theoretical sample. Thus, this calculation includes in the denominator all types of incidents, that is, not only those directly related to the refusal of the selected person to be interviewed, but also to the following incidents:from the sampling frame (e.g., incorrect or unreachable telephone number, or person residing in a place other than the one selected);when conducting the interview (e.g., person who cannot be reached, appointment outside the fieldwork time, or insufficient number of attempts to finish the fieldwork, that is, most would be cases that would have answered the interview if it had been extended to the end of the fieldwork);leaving the cohort (e.g., deceased, long-term hospital admissions, change of residence etc.).

The reason for including all types of incidents in the response rate is to obtain a sufficient theoretical sample size to reach the effective sample size of 3000 interviews. This means that, once almost all the fieldwork of the longitudinal sample had been completed, a new sample was added until the total effective size of 3000 interviews was reached. When that sample size was achieved, the field work was completed at each measurement.

In short, if we take into account only the refusals of the selected person, our total response rates are above 70%. Moreover, the field work carried out has introduced elements of improvement that have allowed for an increase in the response rates from one measurement to the next, both for the longitudinal samples and for the new ones that were incorporated in each measurement.

Thus, for measure 1 of the general ESSOC, the response rate was 88.5%. For measure 2, it was for the longitudinal sample 78.3% and for the new one 58.2% (total 73.0%). For measure 3, it was 88.8% and 75.3%, respectively (total 83.1%), and for measurement 4 it was 91% and 78.2% (total 87.8%, Figure 1). 

### 2.5. Sample Selection and Sample Allocation

The probability sampling method used in each measurement to obtain the ESSOC general sample is the stratified random sampling. Twenty-four strata are defined by eight provinces and three degrees of urbanisation (urban, intermediate density, and rural area) [61] (crossed stratification). Allocation of the new samples for each measurement is proportional to the population size of each stratum of province and degree of urbanisation. This implies that within each stratum (province-degree of urbanisation), any person has the same probability of being selected, that is, self-weighted samples are obtained in each stratum.

In addition, for the M5 measurement, the distribution of the new sample will be performed, in the first place, in the two DA strata and, subsequently, as in the case of the previous measurements.

The theoretical longitudinal sample of a measurement is composed of the effective sample of the previous measurement, except for measurement M1 which, being the first one, does not have a longitudinal sample.

In the ESSOC + 55 sample, the first measurement was stratified by clusters (Guadalinfo Centers, N = 651), with sub-sampling to 1200 users. These centres are stratified per Andalusian province and inhabitation level (<10,000 inhabitants, 10,000–19,999, ≥20,000), as well as sex and age quotas (55–64 years, 65–74 years, and >75 years). As in the case of the ESSOCgeneral sample, the ESSOC+55 second measurement will be made up of a longitudinal sample (that of the first measurement) and another new sample, until a total of 1200 interviews are completed.

### 2.6. Fieldwork

The survey information is collected through a computer-assisted telephone interview (CATI). The management, control, and monitoring of the collection of information is carried out through Pl@teA and MobiNet Gandia Integra software. The data collection is carried out by a team of between 8 and 12 interviewers assigned solely to this study. This ensures working team stability, which is of fundamental importance in regular, longitudinal surveys. Before starting the study, the interviewers will receive the necessary training regarding the content of the survey. To this end, in addition to virtual meetings held before starting the fieldwork, they are provided with interviewer’s and questionnaire manuals which, besides explaining the questionnaire and study’s content, describe the survey platform, possible incidences, and the protocols to be followed in each case to guarantee the maximum quality of the samples and the information collected. Prior to engaging in the fieldwork, each interviewer performs several pilot tests to measure times and determine the complicated points of the questionnaire.

The schedule set to conduct the interviews is from Monday to Friday from 10:00 to 21:00, and on Saturdays from 10:00 to 15:00 for the first measurement, and for the rest of the measurements from Monday to Saturday from 14:00 to 21:00, although deferred appointments can be scheduled without time limits. Furthermore, a telephone line with a 900 prefix and staffed by telephone agents is made available to the public. This number is provided to the survey holders via text message or through the CSyF website, where the characteristics of this study are also published. The call centre also receives calls from people who, after having been contacted by CATI agents, need to confirm the official nature of the survey. In fact, many of these calls become completed interviews.

### 2.7. Quality Control

For the ESSOCgeneral, quality control measures mean the interviews are cross-checked both internally in the call centre itself and in the IECA and EASP. Each interviewer is monitored to ensure that they follow the established protocols and that they use each type of incidence correctly. The intervals elapsed between each call and their duration are also monitored.

In addition to recording the calls made by each interviewer, a ‘listen-in’ check is also performed to review both the positive aspects and those to be reinforced in the supervised interviews (i.e., for 10% of the calls performed for the first measurement and 25% of the calls performed for the rest of the measurements). During these checks, aspects, such as the interviewer’s self-presentation, their presentation of the study, providing the 900-prefix telephone number, confirming the place of residence, the correct delivery of the questionnaire’s questions, and all response options, are assessed.

Quality control, data cleansing, and data coding are carried out simultaneously with the fieldwork with the aid of the software to be used in the study. Each interviewer is provided with a space on the platform to record observations during the survey being conducted. This then allows the supervision team to cleanse those interviews in which the interviewer detected an inconsistency in the respondent’s answers, or those in which the interviewer made a mistake when completing the questionnaire. Likewise, the values of the variables are revised, and invalid ones cleansed. Moreover, the coding of the variables corresponding to open-ended questions, such as the respondent’s occupation and educational level, is carried out in tandem with the fieldwork. In the rest of the open-ended questions, prior to their coding, their possible answers are cleansed, and the categories deemed to correspond to the majority subsequently coded.

During the telephone interviews, different situations may arise that could result in the inability to complete the survey. These are known as field incidences (Table 2), with the most important types being final incidences, i.e., those that, after several attempts, finally result in the inability to complete the survey.

As this is a longitudinal study, one of the most significant reasons for a lack of response is if the potential interviewee identifies the incoming call number and does not answer the phone. To solve this, as much as possible, the telephone number from which each call is made is changed periodically, so that even if a number were to be identified and blocked, we could continue to attempt to contact that person by employing a new telephone number.

In addition to the quality of the sample, there are other factors of interest in assessing how fieldwork has developed during a surveying operation. One such factor is to determine how a survey has been carried out in terms of effectiveness and efficiency. The most direct way to measure this is to calculate the number of attempts or calls that had to be made to complete each survey. This type of information is also very useful to be able to design strategies aimed at optimizing attempts and, therefore, increasing sample levels in future operations.

### 2.8. Sampling Weights

The original sampling weight for the new samples is obtained from the inverse values of the effective sampling fractions in each stratum and used to calculate the Hajek estimator [62]. This is subsequently calibrated to obtain more reliable estimates based on the demographic characteristics of Andalusia. To this end, we use a truncated linear calibration method [63] and, as auxiliary information, the marginals of the Andalusian population per sex and age (16–19, 20–24, 25–29,..., 75–79, and ≥80 years old), sex and province, sex and nationality (Spanish or dual nationality and foreign), and sex and degree of urbanisation. These data are obtained from the Continuous Municipal Register (Padrón Continuo de Municipios) [64]. Regarding the non-response bias in longitudinal samples, we can predict non-contact and non-cooperation based on auxiliary information and information already known about the sample subjects. Thus, the original weights used in the estimates of longitudinal sample M_t are corrected during a first phase by modelling the non-response with respect to the longitudinal effective sample obtained in M_t-1 using machine learning techniques [65]. Said non-response is estimated using a XGBoost model [66], which represents the state-of-the-art in machine learning. Every piece of data and variable from the M_t-1 sample is used for training; thus, the algorithm has all the information available to learn. Likewise, the hyperparameters of the model are optimized using cross-validation to ensure reliable estimations. Then, during a second phase, they are calibrated following the method described for the new samples. As auxiliary variables, we use those extracted from the Continuous Municipal Register (e.g., nationality, sex, age, province, degree of urbanisation, etc.) and the registers from the ESSOC itself in M_t-1 (Table 3).

In addition to these adjustments, other methodological alternatives, not yet explored in this type of sample design, for instance, double calibration, will also be investigated by considering different variables in order to model non-responses and, on the other hand, correction of the representativeness bias [67,68] and machine learning techniques, and adjusting non-responses with the aid of the Propensity Score Adjustment (PSA) [69,70].

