Relationship-situation incidences (reasons that make it impossible to complete the survey due to several types of situations affecting the surveyed people, for instance, they cannot be located, they refuse to participate in the survey, or any other aspect that prevents the survey being conducted).	No contact.	The household cannot be contacted (e.g., nobody answers the telephone, or the answering machine goes off).	Removal after four attempts performed on two different days, at two different times.
	Absent.	The selected person cannot be contacted.	Removal after four attempts performed on two different days and at two different times.
	Inability to answer.	The selected person cannot complete the survey due to an inability to respond to it because of disability, age, illness, lack of knowledge of the language, or any other circumstance. If possible, the survey should be completed by a close relative.	Direct removal.
	Refusal.	The selected person refuses to complete the survey or refuses to continue it after it has begun.	Direct removal.

**Table 3 ijerph-18-08120-t003:** Health Care and Social Survey (ESSOC): Adjustment of the design sampling weight in each measurement.

	Type of Adjustment	
Sample Type (Effective)	1st Phase	2nd Phase
New	Non-response adjusted by proxy based on the effective sample size in each stratum.	Representativeness by truncated linear calibration with 0.1 and 10 limits based on the auxiliary variables
Longitudinal	Non-response adjusted using an XGBoost model based on variables from the previous measurement.	

**Table 4 ijerph-18-08120-t004:** Health Care and Social Survey (ESSOC): Auxiliary sources and variables.

Registry	Description	Information	Variables Extracted
BDLPA–Longitudinal Andalusian Population Database [71]	Information from the census coordination system and civil registries that give rise to a consolidated framework of the Andalusian population	Personal data	Name, surname, identification health number (NUHSA), geographical coordinates
BDU–User Database of the Andalusian Public Health Care System [58]	Contact Information of the Andalusian Public Health Care System	Personal contact information	Telephone numbers

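### As worded, the longitudinal weight restarts from the original weight and models only the latest step of non-response, so earlier panel loss is left to calibration

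*Protocol article*

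**What the plan says.** Section 2.8 defines an original weight once, for people entering the survey: "The original sampling weight for the new samples is obtained from the inverse values of the effective sampling fractions in each stratum". Because this is the effective fraction, non-response at entry is already absorbed by stratum.

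For the longitudinal sample, the same section says that "the original weights used in the estimates of longitudinal sample M_t are corrected during a first phase by modelling the non-response", and it fixes the reference group for that model: "with respect to the longitudinal effective sample obtained in M_t-1 using machine learning techniques". The next step is calibration: "Then, during a second phase, they are calibrated following the method described for the new samples". The auxiliaries are population-register variables and also "the registers from the ESSOC itself in M_t-1 (Table 3").

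Table 3 repeats the scheme. Its title is "Adjustment of the design sampling weight in each measurement", and the first phase of its longitudinal row reads "Non-response adjusted using an XGBoost model based on variables from the previous measurement".

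Section 2.5 sets the panel structure: "The theoretical longitudinal sample of a measurement is composed of the effective sample of the previous measurement". A person seen at M_t as part of the panel has therefore responded at every measurement since entry.

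**The concern.** An M1 entrant interviewed at M4 has passed three selections: M2, M3 and M4. The M4 non-response model is trained on M3 respondents. People lost at M2 or M3 are not in its data, however many M3 variables it uses. If its result multiplies the entry weight, the first two selections have no propensity factor in the final weight.

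The gap falls on a particular set of estimates. Section 2.10 plans changes at each measurement with respect to the first. Within-person change from M1 to M3, M4 or M5 exists only for people with two or more follow-up steps, which is the group whose earlier loss is not modelled. These changes serve the first specific objective, the short- and mid-term impact on health and well-being. The Discussion names panel attrition as a limitation and relies partly on the longitudinal weights to reduce the bias from it.

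**Working it through.** **Reading the two places together.** Section 2.8 has one definition of an original weight (entry, inverse stratum fraction) and one modelled step (M_t-1 to M_t). Table 3 has the design weight and a model on the previous measurement. Neither names the adjusted M_t-1 weight as the base or gives a product of propensities. The two places agree on the one-step reading, but neither explicitly rules out a carried-forward weight.

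**Inputs**
- Longitudinal response rates (section 2.4): M2 78.3%, M3 88.8%, M4 91%. They count refusals only, so they are upper bounds on retention.
- New-sample rates: 58.2%, 75.3%, 78.2%. Totals: 73.0%, 83.1%, 87.8%.
- Target of about 3000 interviews per measurement (section 2.4).
- Retention from M1 to M5 of 25–35% (Discussion).
- Assumption: rates for the mixed panel apply equally to M1 entrants.

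**The plan's own figure.** The effective size reproduces: 1.96² × 0.25 / 0.024² = 1667; × 1.8 = 3001; / 0.6 = 5002, against the stated 3000 and 5000. The concern disputes no stated figure.

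**Share of loss before the last step.** With retention rates r per step, the share is (1 − product of the earlier r) / (1 − product of all r).

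*M4, refusal-only rates.* Retained to M3: 0.783 × 0.888 = 0.695. Retained to M4: 0.695 × 0.91 = 0.633. Share: (1 − 0.695) / (1 − 0.633) = 0.305 / 0.367 = 83%.

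*M4, back-solved from the totals.* Longitudinal share of the denominator = (total − new) / (longitudinal − new). Multiplying by longitudinal / total gives the share of completed interviews.
- M2: 14.8 / 20.1 = 0.736; × 78.3 / 73.0 = 0.790
- M3: 7.8 / 13.5 = 0.578; × 88.8 / 83.1 = 0.617
- M4: 9.6 / 12.8 = 0.750; × 91 / 87.8 = 0.777

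With 3000 interviews each time, these are also the step retentions. Retained to M3: 0.488. Retained to M4: 0.379. Share: 0.512 / 0.621 = 83%. The two routes disagree on the level of retention (63% and 38%) but agree on the share.

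*M5, equal steps.* 0.25^(1/4) = 0.707, share (1 − 0.707³) / 0.75 = 86%. 0.35^(1/4) = 0.769, share (1 − 0.769³) / 0.65 = 84%.

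*M5, refusal-only rates to M4.* This is the smallest early loss that fits the stated rates. 0.367 / 0.75 = 49%; 0.367 / 0.65 = 57%.

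**Who is affected at M4.** About 62% of the M3 effective sample was longitudinal (0.617 above). If they return at M4 at the same rate as the others, about 62% of the M4 panel has at least one unmodelled earlier step. The other 38% entered at M3 and need only the one step that is modelled.

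**The case against.** **The wording.** The definition of the original weight is given for new samples only. In the longitudinal sentence the phrase could mean the weight that enters step M_t, already adjusted at M_t-1. The title of Table 3, with its reference to each measurement, can be read the same way, and the Discussion speaks of adjustments in each measurement. This stands as a possible reading. It does not remove the point, because the article's own definition and the word design in Table 3 point the other way and no sentence states the chaining.

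**Calibration.** The second phase uses M_t-1 survey variables as well as register margins. If the targets are weighted M_t-1 estimates, part of the earlier correction may be carried forward. Double calibration and propensity score adjustment are also to be investigated. This stands in part: calibration may recover some of the earlier loss for outcomes related to the auxiliaries, but it does not replace the earlier propensities.

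**The rates.** The back-solve is fragile. At M2 it implies 0.790 × 3000 / 0.783 = 3026 longitudinal completions plus refusals, more than the roughly 3000 M1 respondents available. Carried to M5 it would put only 4–17% of the loss at the last step, which the refusal-only bound (43–51%) does not support. For this reason M5 is given as a wide range.

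**A tempting stronger reading.** A reader might infer a bias of several points, larger than the planned precision. If 25% were in poor health and responded 5 to 10 points less at each step, the back-solved rates with only the last step corrected would leave that group's share at M4 short by 2.7 to 5.2 points. The document does not support using this as the size of the harm. The prevalence and response gaps are assumed, calibration is ignored, and the result is a group share and not a change. If the change differed by 10 points between the groups, the bias in mean change would be 0.27 to 0.52 points. The 2.4 points is a cross-sectional precision and no yardstick for a panel change.

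**Conclusion.** The concern holds in a limited form. As worded, section 2.8 and Table 3 apply one step of modelled non-response to the original weight. For participants with two or more follow-up steps, earlier selective loss is then left to calibration.

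The loss outside the model is most of the total for M1 entrants at M4 (about 83%) and between about half and most at M5 (49–57% to 84–86%). These figures assume that mixed-panel response rates apply to M1 entrants. They are shares of loss, not of bias: loss unrelated to the outcome does no harm. The size of any bias in the change estimates cannot be derived from the document.

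A reader might also infer that the M3 and M4 weights were in fact built wrongly, or that the whole panel is affected. The document shows neither. It does not report how the weights were computed, and people who entered at M_t-1, like the M2–M1 comparison, involve a single step that the plan models.

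**What to change.** State in section 2.8 that the base weight for the M_t longitudinal sample is the adjusted M_t-1 weight multiplied by the inverse of the estimated M_t response propensity, so that it carries the product of all steps since entry, and that calibration follows. Retitle Table 3 to match.

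If the M3 and M4 weights were already built this way, the change is one of wording. If not, recompute them from the data in hand, check the spread of the weights and trim if needed. M5 can follow the same rule. The cost is the recomputation and somewhat more variable weights, with some loss of precision in the panel estimates.

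### Longitudinal attrition weights appear to rest on in-sample XGBoost response probabilities; out-of-fold prediction would modestly reduce the bias left, at almost no cost

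*Protocol article*

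**What the plan says.** Section 2.8 weights the longitudinal sample in two phases. In the first, the original weights are "corrected during a first phase by modelling the non-response with respect to the longitudinal effective sample obtained in M_t-1", using XGBoost. On the training data the article states: "Every piece of data and variable from the M_t-1 sample is used for training; thus, the algorithm has all the information available to learn". On model complexity it adds that "the hyperparameters of the model are optimized using cross-validation to ensure reliable estimations". Table 3 summarises the phase as "Non-response adjusted using an XGBoost model based on variables from the previous measurement".

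On the second phase the article says: "Then, during a second phase, they are calibrated following the method described for the new samples". Table 3 describes it as "Representativeness by truncated linear calibration with 0.1 and 10 limits based on the auxiliary variables". For the longitudinal samples the auxiliary variables are register margins and also ESSOC information from the previous measurement; the article does not list which survey variables these are.

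New samples are treated differently. Their first phase uses the achieved sample per stratum, with no XGBoost model. The section also says that "other methodological alternatives, not yet explored in this type of sample design, for instance, double calibration, will also be investigated".

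**The concern.** The probabilities are needed for the members of the M_t-1 sample, and those same members train the model. A boosted-tree fit has already seen each person's response status, so its predictions for them are pulled towards 1 for respondents and towards 0 for non-respondents. Cross-validated tuning limits how far this goes, but it only selects the settings. The final fit on all cases is still in-sample when it predicts those cases. The article presents training on everything as a strength and says nothing about holding a person out when that person's probability is predicted.

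A respondent with a dropout's profile then gets too high a probability and too small an inverse weight, so the correction for attrition falls short. Longitudinal estimates from M2 onwards carry these weights, and the shortfall can add up over successive measurements.

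**Working it through.** **Design figure.** Section 2.4 gives p = 0.5, precision 2.4 points, 95% confidence, design effect 1.8 and non-response 40%.
- n = 1.96² × 0.25 / 0.024² = 1667.3
- × 1.8 = 3001 effective
- / (1 − 0.40) = 5002, against 5000 stated. The figure reproduces.

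For later measurements "the aim for the subsequent ones is to reach an effective sample about 3000 people per measurement". The training set is therefore about 3000 people.

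**Attrition per step.** Section 2.4 reports longitudinal response of 78.3%, 88.8% and 91% (M2 to M4), but the Figure 1 caption says these count refusals only, while section 2.8 models non-contact as well. The Discussion expects 25–35% of the M1 effective sample to remain at M5. Over four steps that is 0.25^(1/4) = 0.71 to 0.35^(1/4) = 0.77 per step. The simulations cover 60% to 90%.

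**Estimator.** Respondents get w = 1/p̂ and the estimate is Σwy/Σw. In-sample p̂ is compared with cross-fitted p̂, both from models tuned by cross-validation. n = 3000 in A to D. Covariate, selection and outcome effects are assumed, because the article gives none.

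**Mechanism (A).** Mean predicted probability:
- Non-respondents: 0.577 in-sample, 0.679 out-of-fold, 0.642 true.
- Respondents: 0.807 in-sample, 0.780 out-of-fold, 0.786 true.
- In-sample inverse weights sum to 95–97% of the issued sample; cross-fitted ones sum to 100%.

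**Size of bias, percentage points (absolute values).** Gains are differences of rounded figures.

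| Setting | Response | Calibration | Unweighted | In-sample | Cross-fitted | Gain |
|---|---|---|---|---|---|---|
| A, 50 covariates, stronger selection | 75% | none | 3.7 | 1.8 | 1.1 | 0.7 |
| A, weaker selection | 75% | none | 2.4 | 1.3 | 1.0 | 0.3 |
| B, 30 covariates, tuned on log-loss | 60% | none | 4.41 | 1.32 | 1.05 | 0.27 |
| B | 78% | none | 2.53 | 0.90 | 0.78 | 0.12 |
| B | 90% | none | 1.17 | 0.44 | 0.40 | 0.04 |
| B, tuned on accuracy | 60% | none | 4.35 | 1.03 | 0.79 | 0.24 |
| B | 78% | none | 2.32 | 0.43 | 0.30 | 0.13 |
| B | 90% | none | 1.17 | 0.30 | 0.22 | 0.08 |
| B, 150 covariates, log-loss | 60% | none | 4.69 | 1.92 | 1.71 | 0.21 |
| C, 100 covariates, step 1 of 4 | 35% over 4 steps | demographic | – | 0.82 | 0.77 | 0.05 |
| C, step 4 of 4 | 35% over 4 steps | demographic | – | 2.66 | 2.53 | 0.13 |
| D, 50 covariates, stronger selection | about 77% | none | 5.20 | 2.01 | 1.54 | 0.47 |
| D | about 77% | demographic | 5.20 | 1.79 | 1.39 | 0.40 |
| D | about 77% | plus M_t-1 variables | 5.20 | 0.92 | 0.88 | 0.04 |
| D, weaker selection | about 77% | none | 3.23 | 1.34 | 1.16 | 0.18 |
| D | about 77% | demographic | 3.23 | 1.15 | 1.00 | 0.15 |
| D | about 77% | plus M_t-1 variables | 3.23 | 0.53 | 0.51 | 0.02 |
| E | 60% | no M_t-1 variables | – | 1.83 | 1.39 | 0.44 |
| E | 77% | no M_t-1 variables | – | 1.19 | 0.97 | 0.22 |
| E | 90% | no M_t-1 variables | – | 0.43 | 0.40 | 0.03 |

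In E, calibrating on M_t-1 survey variables as well brought the gain to about 0.02–0.26 points. Replicates: 30 in A, 80 in B (16 with 150 covariates), 40 in C and 25 per scenario in D. The Monte Carlo standard error in B's tuned 30-covariate runs is 0.02–0.09. The smallest gains in D should not be read as precise.

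**Accumulation.** In C the paired gain grows over the four steps: 0.05, 0.08, 0.10, 0.13 (standard error 0.01–0.02).

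**Source of the remainder.** In B's tuned 30-covariate runs, weighting by the true probabilities left only −0.12 to 0.09 points, so the residual comes from estimating the probabilities. Cross-fitting takes away 0.04/0.44 = 9% to 0.13/0.43 = 30% of it there, and 0.7/1.8 = 39% in A. The larger part persists out-of-fold, as expected from a regularised fit.

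**The case against.** The article states which data train the model, not which predictions enter the weights. In K-fold cross-fitting every case also serves for training, so the quoted sentence does not rule it out, and a condensed article may leave this detail to the full plan. Fitting on the whole sample and weighting the same cases is the usual way to build non-response weights. Tuning by cross-validation is the standard guard against overfitting. The second phase also calibrates on previous-wave survey variables, and the authors promise to study alternatives. Much of this stands: the in-sample reading is an inference, and the planned calibration absorbs part of the effect, nearly all of it in D. It does not make tuning equivalent to out-of-fold prediction.

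Four stronger readings are tempting and not supported:
- A reader might infer that the probabilities are badly overfitted and the correction fails. With tuning, in-sample weights in B's 30-covariate runs still removed 62% to 81% of the unweighted bias. They left nearly all of it only when the model was untuned, which is not the plan.
- A reader might infer that cross-fitting would remove the bias. It removed 66% to 87% in the same runs.
- A reader might infer that every M2 to M5 estimate is affected. The new samples get no XGBoost adjustment.
- A reader might infer that calibration is demographic only and cannot help. Section 2.8 also names ESSOC information from M_t-1.

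**Conclusion.** The point holds as a low-severity improvement. On the plain reading of section 2.8 the response probabilities are in-sample, and attrition in the longitudinal weights is then slightly under-corrected. In every simulation with tuned models cross-fitting left less bias; where RMSE was computed it was also lower (for example 1.52 to 1.32 in B at 60% response, 1.07 to 1.04 in D after full calibration).

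The gain is roughly 0.03–0.7 points before calibration and 0.02–0.3 points after calibration that includes M_t-1 survey variables. Against the stated 2.4-point precision the upper ends are 0.7/2.4 = 29% and 0.3/2.4 = 12.5%; most scenarios lie well below. Most of the remaining bias comes from regularisation and would stay.

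These sizes rest on assumed effects, on assumed calibration variables (the article does not list them), and on the inference that predictions are in-sample.

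**What to change.** In section 2.8, replace the sentence on training data by a statement that hyperparameters are tuned by cross-validation and that each person's response probability is predicted from folds excluding that person (cross-fitting with 5 to 10 folds). Keep the tuning: in B's untuned runs cross-fitting over-corrected, with RMSE 6.12 against 4.09 at 60% response and 2.50 against 2.32 at 78%.

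Add two checks before calibration, because calibration resets the totals: the respondents' inverse probabilities should sum to about the issued longitudinal sample, and the M_t-1 variables should balance after weighting.

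Recompute the M2 to M4 longitudinal weights from the existing data and use the same rule for M5, or confirm that out-of-fold predictions were already used. The only cost is a few lines of code and re-running it; no new data are needed.
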